## Abstract

**Introduction:**

Exercise is a cornerstone of type 2 diabetes (T2DM) management, yet individuals exhibit vast inter-individual variability in glycemic response to interventions. Gut microbial diversity and exercise intensity may be factors influencing this response variability. However, the interplay between exercise intensity, microbial adaptations, and glycemic outcomes in individuals living with T2DM remains unclear.

**Objectives:**

The purpose of this protocol is to describe the GUTFIT study, which aims to test whether performing vigorous-intensity combined aerobic and resistance training produces greater changes in glycemia and gut microbial diversity than moderate-intensity training in individuals living with T2DM. A secondary objective is to explore whether decreases in glycemia after exercise are associated with alterations in gut microbial community architecture and diversity.

**Methods:**

The GUTFIT Study (NCT06268743) is a parallel-group, single-blinded, randomized trial involving 40 adult participants (n = 20 female) living with T2DM. Participants will be randomized to 16 weeks of: 1) vigorous-intensity exercise (aerobic training at 70–80% heart rate reserve and resistance training at 8–10 repetitions of 75–80% maximal strength) or 2) moderate-intensity exercise (aerobic training at 45–55% heart rate reserve and resistance training at 12–15 repetitions of 65–70% maximal strength). Glycemia will be measured via glycated hemoglobin (HbA1c), and gut microbial composition will be determined in participant fecal samples using next-generation sequencing (Illumina MiSeq) of 16S ribosomal DNA genes. All outcome measures will be tested pre- and post-intervention.

**Discussion:**

Results of this study will provide further insight into the role of exercise intensity in changes in glycemia and the gut microbiome, and whether there is an intensity-dependent association between exercise-induced changes in glycemia and gut microbial diversity in individuals living with T2DM.

## Introduction

As global rates of type 2 diabetes mellitus (T2DM) and its related complications continue to rise, there is a growing need for more effective lifestyle interventions [1]. Exercise is a well-established intervention for managing T2DM, primarily due to its capacity to enhance insulin sensitivity, thereby improving glycemia and mitigating disease-related complications [2–4]. However, considerable inter-individual variability exists in the metabolic response to exercise. While some individuals demonstrate marked improvements in glycemia and insulin sensitivity, others show little to no benefit, despite comparable adherence to prescribed programs [5,6]. This variability underscores the need to identify modifiable factors that influence individual responsiveness to exercise interventions in an effort to optimize exercise prescriptions for T2DM management.

Several factors have been proposed to account for this response heterogeneity, including variation in training modality, intensity, volume, or duration, baseline metabolic health, and genetic predisposition [7]. Among these, exercise intensity has received particular attention, as it can be manipulated to potentially enhance exercise effectiveness [7,8]. Nevertheless, recent findings suggest that modifying aerobic exercise intensity alone does not consistently resolve non-responsiveness in glycemic outcomes among individuals with prediabetes or T2DM [6]. These observations suggest that other mechanisms may mediate the metabolic benefits of exercise.

The gut microbiome has gained recent attention as a key regulator of metabolism and glucose homeostasis, with potential implications for modulating individual responses to exercise [5,7,9–14]. Regular physical activity is associated with increased microbial diversity and a shift towards a microbiota profile enriched with beneficial taxa [15–20]. In individuals living with T2DM, these exercise-induced microbial alterations may have clinically relevant implications as they are linked to improved glycemia and reduced systemic inflammation, addressing key pathophysiological features of the disease [12,13,21,22].

Emerging evidence suggests a bidirectional relationship between exercise and the gut microbiome: while exercise alters microbial composition, baseline gut microbiota profiles may, in turn, modulate the glycemic response to exercise [5,13,23]. For instance, Liu et al. (2020) found that differential alterations in gut microbiota composition were strongly correlated with glycemic response to exercise in men living with prediabetes following an exercise intervention [5]. Their analysis further revealed that microbial capacity for metabolite production increased in exercise responders, and that distinct baseline gut microbial signatures predicted exercise responsiveness for glycemic outcomes [5]. These findings suggest that gut microbial profiles may serve as biomarkers of exercise responsiveness and offer novel insight into the mechanisms underlying inter-individual variability in metabolic outcomes.

Exercise modality and intensity have been proposed as factors that modulate exercise response in T2DM via gut microbiome alterations. Higher-intensity exercise has been associated with greater shifts in microbial diversity [24,25], which may amplify the production of short-chain fatty acids (SCFAs) and other metabolites that improve insulin sensitivity and glucose regulation [12,14]. In 2023, Torquati et al. showed that eight weeks of moderate-intensity continuous training and high-intensity interval training resulted in distinct changes in gut microbial community composition and the relative abundance of specific health-promoting taxa between the intensity groups [26]. However, these microbial adaptations did not translate into significant between-group differences in glycemic outcomes or gut-derived metabolites such as SCFAs, suggesting that the link between exercise intensity, gut microbial adaptations, and glycemic regulation remains equivocal [26]. Exercise modality can also induce distinct microbial modifications in the gut [9]. While aerobic exercise is well-documented for its ability to enhance the abundance of SCFA-producing bacteria, which are known to improve insulin sensitivity and reduce inflammation [16,23–25,27,28], resistance training may promote microbial diversity and complement aerobic exercise effects [23,24,29], suggesting that combined interventions could maximize the microbiota-mediated benefits for metabolic health [9,15,24,30,31].

To date, the majority of research surrounding exercise and the gut microbiome has focused on healthy populations, with limited data exploring the interplay between exercise intensity, microbial adaptations, and glycemic outcomes in individuals living with T2DM. Investigating these relationships could provide valuable insights into optimizing exercise prescriptions and addressing inter-individual variability in T2DM management. As such, the primary objective of this study is to determine whether performing combined aerobic and resistance training at a vigorous intensity improves glycemia, measured by hemoglobin A1c (HbA1c), and increases gut microbial diversity compared to performing combined training at a moderate intensity. We hypothesize that individuals exercising at a higher intensity will experience greater reductions in HbA1c and more significant alterations in gut microbial community structure, with greater increases in gut microbial diversity, than individuals training at a lower intensity.

## Materials and methods

### Study design

The GUTFIT Study is a parallel-group, single-blinded, randomized trial.

### Study setting

The GUTFIT study (NCT06268743) will be conducted in the Cardiometabolic Exercise and Lifestyle Laboratory (CELLAB) in the Faculty of Kinesiology at the University of New Brunswick in Fredericton, Canada. This location was selected for its private gym facility, availability of necessary equipment, and access to research staff who are experts in clinical trial delivery and trained to work with individuals living with T2DM.

### Eligibility criteria

#### Inclusion criteria.

Community-dwelling adults aged 19 years and older.Currently living with T2DM, confirmed by a glycated hemoglobin (HbA1c) value of ≥ 6.5% or diagnosed by a physician with T2DM with an HbA1c of ≥ 5.7%.Not currently partaking in regular physical activity, defined as 150 minutes of moderate-to-vigorous aerobic activity and two or more days of resistance training per week as per the 24-Hour Movement Guidelines [32], or averaging >10,000 steps per day over a five-to-seven-day period at baseline.

#### Exclusion criteria.

Diagnosed with low iron concentration, anemia, or currently being treated for these conditions.Diagnosed with any red blood cell-altering conditions.Diagnosed with any cardiovascular disease that would impact the ability to safely participate in exercise training.Currently prescribed any medication that would impact the ability to use a heart rate monitor to accurately track exercise.Diagnosed with any gut microbiome-altering conditions (e.g., Celiac disease, GERD, irritable bowel syndrome (IBS), or inflammatory bowel disease (IBD)).Currently taking any gut microbiome-altering supplements (prebiotics/probiotics) or report taking antibiotics throughout the trial.Unstable T2DM medication over the past 3 months.

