#### Secondary outcomes.

Demographics, family medical history, and current medication usage will be recorded by research staff for all participants during baseline testing. Participants will be monitored throughout the study and asked to report any changes in medication use to research staff. Medication usage will be confirmed through detailed label inspection or a pharmacy printout at baseline and post-testing. To confirm and record participants’ physical activity levels for eligibility criteria, participants will complete the Get Active Questionnaire [36] and wear a Fitbit Charge 3 pedometer (Fitbit Inc., San Francisco, California, USA) for a 5–7-day period between the first and second baseline testing visits, over which their daily step count will be averaged, and the participant eligible if the average is < 10,000 steps per day.

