Muscular strength will be assessed through 1-repetition maximum (1-RM) testing for each of the weighted exercises performed throughout the program, excluding abdominal crunches. Participants will perform two warm-up sets: the first with a weight they can complete 6–10 repetitions with, and the second with a weight they can complete 3–5 repetitions with. Following the warm-up sets, research staff will increase the weight until participants can no longer lift the weight or show improper form during the movement. Rest periods between maximal attempts will be 1–3 minutes. There will be a maximum of seven attempts to reach the 1-RM. If the 1-RM is not reached, the participant will repeat testing for that exercise during their first exercise session, following the same protocol.

The gut microbiome will be analyzed using next-generation sequencing (Illumina MiSeq) of 16S ribosomal DNA genes. Participant fecal samples will be collected using OMNIgene®•GUT fecal sample collection kits (DNA Genotek Inc., Ontario, Canada) to ensure high-quality preservation of the microbial community structure. Participants will receive detailed instructions for collecting the sample and will be provided with a collection kit to use at home on the day before their first exercise session and after their last exercise session. Once collected, samples will be pipetted into microcentrifuge tubes and stored at −80 °C until the end of the intervention for batch analysis.

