### Randomization

Randomization of the intervention participants will occur following completion of the second baseline testing visit using a 1:1 allocation ratio, stratified by sex, in a balanced randomized block design performed in sealed envelope software [51]. A member of the CELLAB staff who is not related to the project and has no contact with participants will hold the password-protected randomizations. When a new participant completes baseline testing and is ready for their first exercise session, the participant’s ID number and sex will be sent to the member of staff responsible for randomization via email, who will respond to research staff with the participant’s randomization (moderate or vigorous).

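### The antibiotic and supplement exclusion sets no interval before the baseline stool sample, so recovery from a recent course can enter the measured change in gut diversity

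*Protocol article*

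**What the plan says.** Antibiotics appear once in the protocol article, under Exclusion criteria: "Currently taking any gut microbiome-altering supplements (prebiotics/probiotics) or report taking antibiotics throughout the trial". The supplement part concerns use at the time of screening, and the antibiotic part concerns use during the trial. The next criterion in the list looks back in time, but only for diabetes drugs: "Unstable T2DM medication over the past 3 months".

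Under Secondary outcomes, the medication record is of what is being taken at the time: "Demographics, family medical history, and current medication usage will be recorded by research staff for all participants during baseline testing". Changes during the study are to be reported, and "Medication usage will be confirmed through detailed label inspection or a pharmacy printout at baseline and post-testing".

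The microbiome is sampled twice, with a "collection kit to use at home on the day before their first exercise session and after their last exercise session".

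Two objectives rest on these samples. The Introduction puts into the primary objective whether vigorous training "increases gut microbial diversity compared to performing combined training at a moderate intensity". The Abstract's secondary objective is to "explore whether decreases in glycemia after exercise are associated with alterations in gut microbial community architecture and diversity". The Primary outcome section names HbA1c alone as the primary outcome. Allocation is made "using a 1:1 allocation ratio, stratified by sex, in a balanced randomized block design".

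**The concern.** By listing antibiotics beside supplements that alter the microbiome, the protocol treats them as a disturbance to be kept out of the data. The rule protects the two stool samples unequally. The second sample follows 16 weeks in which antibiotic use is grounds for exclusion. The first has no stated antibiotic-free or supplement-free interval before it, apart from any days between consent and sampling.

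If someone enters while the microbiome is still recovering from a course, the recovery falls between the two samples and looks like a response to training. Both arms exercise, so no untrained group would reveal it. Three results are exposed, in different ways:

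- **Pooled pre-post change in diversity:** biased directly.
- **Association between HbA1c change and diversity change:** gains variation that has nothing to do with exercise.
- **Between-arm contrast in diversity:** gains variance and is open to chance imbalance in small arms.

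**Working it through.** **1. Does any other text close the gap?**

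- Consent is given at the first baseline visit (Informed consent). The second visit is about a week later (Secondary outcomes), and training starts within 1 week of completing baseline testing (Intervention). If the trial is taken to begin at consent, antibiotics in roughly the last one to two weeks before the stool sample are already covered.
- A course completed before consent meets no exclusion criterion. A supplement stopped before screening is not current use, so it meets none either.
- The baseline record is of current medication. Label inspection shows products in hand. A pharmacy printout might show a finished course, but it is an alternative to label inspection and need not exist for everyone.

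The gap therefore remains for use that ended before consent or screening.

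**2. The plan's own sample size, to obtain a scale.** Inputs from Statistical analysis: effect size 0.30, alpha 0.05, power 0.80, n = 24 (12 per group), dropout up to 40%, 40 recruited.

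- Dropout: 24 / (1 − 0.40) = 40, as stated.
- If 0.30 were a standardized mean difference, a two-sided two-sample comparison would need 175 per arm (138 one-sided). That does not give 12.
- If 0.30 is Cohen's f for the group-by-time interaction with 2 groups and 2 time points, the noncentrality is λ = f² × N × 2 / (1 − ρ). With ρ = 0.5 (assumed, not stated), λ = 0.09 × 24 × 2 / 0.5 = 8.64 on 1 and 22 df. Power is 0.802 at N = 24 and 0.763 at N = 22, so the stated 24 is reproduced.
- In SD of change, a two-group comparison has λ = d² × n / 2 with n = 12 per arm. Setting 6d² = 8.64 gives d = √1.44 = 1.2. Under this reading the stated n corresponds to a difference of about 1.2 SD of change.

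**3. Effect of one recent user.** Assumption: diversity rebounds by k = 2 to 3 SD of the usual change. The documents give no figure. The shift in that arm's mean is k / n.

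| | 12 per arm | 20 per arm |
|---|---|---|
| k = 2 | 2/12 = 0.17 SD | 2/20 = 0.10 SD |
| k = 3 | 3/12 = 0.25 SD | 3/20 = 0.15 SD |

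As a share of 1.2 SD: 0.17/1.2 = 14%, 0.25/1.2 = 21%, 0.10/1.2 = 8% and 0.15/1.2 = 13%.

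**4. Milder and more frequent disturbance.** Assumption: a share p of the 40 are recent users, each with a recovery of s SD. The pooled mean change shifts by p × s. The SD of change is multiplied by √(1 + p(1 − p)s²). Power is for a between-arm difference that has 80% power at 20 per arm without disturbance.

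| p (people) | s | Pooled shift (SD) | SD multiplier | Power |
|---|---|---|---|---|
| 5% (2) | 0.5 | 0.025 | 1.006 | 79.5% |
| 10% (4) | 1 | 0.10 | 1.044 | 76.5% |
| 20% (8) | 2 | 0.40 | 1.281 | 59% |

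**5. Chance imbalance.** With 40 people split 20:20 (ignoring the sex strata), the arms differ by at least 2 recent users with these probabilities:

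- 2 users: 2 × C(20,2) / C(40,2) = 380/780 = 49%.
- 4 users: 1 − C(20,2)² / C(40,4) = 60%.
- 8 users: 1 − C(20,4)² / C(40,8) = 70%.

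An excess of 2 users in one arm moves the contrast by 2 × 1/20 = 0.10 SD if each shifts by 1 SD.

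**The case against.** Recent use precedes a 1:1 random allocation, so it is expected to be equal in the two arms, like any covariate that is not stratified. The named primary outcome is HbA1c, which this does not touch. Both the frequency of recent use and the size of recovery are supplied here, and at the mild end (5% of participants, 0.5 SD) power falls only from 80% to 79.5%. The 3-month criterion concerns stability of diabetes medication, so it does not show that the same window was owed for antibiotics. A sensitivity analysis may already be in an analysis plan that is not shown.

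Most of this stands and limits the point. It does not remove it. The article prints the criterion with its own time frames, so this is not detail left to a fuller document, and the diversity comparison is written into the primary objective.

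Two stronger readings are tempting and are not supported:

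- **The vigorous-versus-moderate contrast is systematically biased.** Randomization rules that out in expectation. The harm to that contrast is noise and chance imbalance.
- **One recent user could account for a third to five sixths of the planned effect.** This follows only if 0.30 is read in SD units (0.10/0.30 to 0.25/0.30). That reading needs 175 per arm and cannot yield the stated 12. The reading that reproduces 24 puts the share at 8 to 21%. The protocol also does not tie 0.30 to diversity.

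**Conclusion.** The point holds as a minor design weakness. The criterion leaves the baseline stool sample unprotected against courses finished before consent and supplements stopped before screening, and the stated medication record need not reveal them. The consequence is direct bias in the pooled diversity change, extra variation in the association with HbA1c, and added variance and chance imbalance in the randomized diversity contrast.

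The size is illustrative. The 8 to 21% range rests on an assumed rebound of 2 to 3 SD, on 12 to 20 analysed per arm, and on a planning effect of about 1.2 SD that itself requires f = 0.30 and ρ = 0.5. With rare and mild disturbance the loss is negligible. With 20% recent users and a 2 SD recovery, power would fall from 80% to 59%. The documents cannot say where in that range the trial lies, which is the reason to record the exposure.

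**What to change.** 1. Ask every participant, including those already enrolled, for the date of the last antibiotic course and of any prebiotic or probiotic use before the baseline stool sample. Check against the pharmacy printout where one exists. Non-prescription supplements may not appear on it, so the question is still needed.
2. Before results are seen, specify a sensitivity analysis of the diversity outcomes and of the HbA1c-diversity association that excludes recent users or adjusts for recent use.
3. For participants still to be recruited, add a pre-baseline window to the exclusion criterion or defer the baseline sample. The length of the window is for the investigators to set and justify. The 3 months in the diabetes-medication criterion serve another purpose.

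The cost is one question and one additional analysis. Recall will be imperfect for people enrolled since April 2024. A few late recruits may be deferred, and a criterion changed late means that the sample was enrolled under two rules, which the report should state. The HbA1c analysis is unchanged.

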### Recruitment

The GUTFIT study is currently recruiting participants from the city of Fredericton and the Greater Fredericton Area via social media and radio advertisements, as well as advertisements placed in pharmacies, healthcare centers, physician offices, and community organizations. Further recruitment is occurring through electronic communication, including e-newsletters within various organizations and groups. Participants from previous studies who expressed interest in being considered for future research have also been contacted. Recruitment began on February 29th, 2024, with the first participant enrolled on April 3^rd^, 2024. Recruitment is expected to be completed by March 2026, and the anticipated completion date of all data collection and follow-up visits is June 2026. Results from this study are anticipated to be available by January 2027.

### Intervention

Eligible participants for the GUTFIT study will be randomized into one of two intervention arms: 1) moderate-intensity exercise, or 2) vigorous-intensity exercise.

Participants in both intervention groups will be randomized and scheduled to begin exercise sessions within 1 week of completing all baseline testing. The 16-week training protocol requires participants to perform two resistance-training sessions per week and at least two aerobic exercise sessions per week. All exercise sessions will be supervised by research staff and take place in an exercise facility located in the CELLAB. To maximize adherence to the intervention, exercise sessions are scheduled on a weekly basis, with research staff available 7 days a week.

#### Resistance training.

The resistance training component of the intervention involves eight resistance exercises: seated chest press, triceps extension, lat pull-down, leg press, knee extension, and knee flexion using Atlantis Strength weight machines; seated shoulder press with dumbbells; and unweighted abdominal crunches. Resistance training sessions will occur twice per week on non-consecutive days. The moderate-intensity group will perform resistance training at 65–70% of the one-repetition maximum (1RM) for one set of 12–15 repetitions per exercise. The vigorous-intensity group will perform the resistance training at 75–80% of the 1RM for one set of 8–10 repetitions. Participants’ prescribed weight for an exercise will be increased if they successfully complete the maximum number of repetitions of an exercise in two consecutive sessions. Abdominal crunches will remain unweighted for the duration of the intervention. If a participant is unable to perform an abdominal crunch, they will start with seated chair crunches and progress to full abdominal crunches as they are able.

